## 3.9. Statistical methods

### 3.9.1. Outcomes

To examine the possibility of selection bias, a comparative analysis of respondents and non-respondents will be conducted based on demographic and clinical data. Estimates of the prevalence of depression, anxiety, and other mental comorbidity in the target population will be reported as unadjusted raw rates observed in the total sample. Descriptive statistical analysis will be conducted for all data. Temporal changes in scales will be investigated by calculating differences between time-points. Comparisons of demographic and other factors will be conducted using the t-test and ANOVA, and Kruskal-Wallis test. Associations between variables will be examined using correlation analysis, chi-squared tests and regression analysis, depending on the presence or absence of depression and anxiety based on outcome scores. Multiple or logistic regression analysis will be used to adjust for the effects of confounders and to identify predictors of outcome. All analyses will be performed using IBM SPSS Statistics Version 26.

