# 1. TRIAL SUMMARY

World Health Organization Registration Data Set

| Title | Prevalence of psychological distress, quality of life, and satisfaction among patients and family members following comprehensive genomic profiling testing: Protocol of the Quality of Life for Cancer genomics and Advanced Therapeutics (Q-CAT) Study |
| --- | --- |
| Primary registry and trial identifying number | Japan Registry of Clinical Trials: RCT1030200039 |
| Sources of monetary or material support | This work is supported by Japan Society for the Promotion of Science (JSPS) grant number 20K21742 and Daiwa Securities Health Foundation. |
| Central contact | [name], PhD  National Cancer Center Hospital  [name]  [contact] [name] |
| Study officials/Investigators | [name]  National Cancer Center Hospital  [name]  [contact], [name]  [contact]  Study Principal Investigator |
| Brief title | Protocol of the Quality of Life for Cancer genomics and Advanced Therapeutics (Q-CAT) Study |
| Acronym | Q-CAT |
| Countries of recruitment | Japan |
| Interventions | None |
| Key eligibility criteria | Age eligibility: No limit  Sex eligibility: Both  Accepts healthy volunteers: No  Inclusion criteria:  1. Patients at National Cancer Center Hospital  2. Patients pathologically diagnosed as malignant solid tumor  3. Patients planned to perform comprehensive cancer genome profiling  4. Patients with written informed consent  5. Family member of patients consented to this trial  6. Family member of patients who also attend the appointment for result of comprehensive cancer genome profiling  7. Family member of patients with written informed consent  Exclusion criteria:  1. Patients with difficulty writing and reading Japanese  2. Patients who was others judged by the investigator to be unsuitable for the study  3. Family member of patients with difficulty writing and reading Japanese  4. Family member of patients who was others judged by the investigator to be unsuitable for the study |
| Study design | Primary purpose: Supportive Care  Phase: Observational study |
| Date of first enrollment | May 18, 2020 |
| Target sample size | 500 |
| Recruitment status | Ongoing |
| Primary outcomes | Outcome: Prevalence of depression  Timeframe: at before comprehensive cancer genome profiling test, at the time of explanation of the result, at three times after the test, at the six months after the test |

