## 3.4. Outcomes

Primary outcome:

Depression

The nine items of Patient Health Questionnaire-9 (PHQ-9) [Spitzer et al., 1999] will be used to measure depression. Higher scores indicate greater possibility of major depression (a PHQ-9 score ≥10, the cut off score, had a sensitivity of 88% and a specificity of 88% for major depression).

Secondary outcomes:

Anxiety

The seven items of General Anxiety Disorder-7 (GAD-7) [Spitzer et al., 2006] will be used to measure anxiety. Higher scores indicate greater possibility of generalized anxiety disorder (a GAD-7 score ≥10 had a sensitivity of 89% and specificity of 82% for generalized anxiety disorder).

QOL

The 30 items of the European Organization for Research and Treatment of Cancer Quality of Life Questionnaire module Core 30 (EORTC QLQ−C30) [Aaronson et al., 1993] will be used to measure QOL. For global QOL scale and functional scales, higher score indicates a better level of function. For symptom-oriented scales, higher scores indicate more severe symptoms.

Symptoms

The nine items of the Edmonton Symptom Assessment System (ESAS) [Yokomichi et al., 2015] will be used to measure symptoms. High scores indicate greater morbidity.

Qualitative interviews

All participants with a PHQ-9 score above cut-off, and a small convenience-selected subset of participants will be invited at baseline and at each follow-up time-point to participate in structured interviews based on SCID-IV [JAMA, 2015].

Knowledge

A 10-item, multiple choice, study-developed questionnaire will be used to assess knowledge of the purpose of CGP testing, likely frequency of informative results, cancers in which informative results are more likely to be found, availability of tailored treatment options, and source of genetic knowledge. Scores will be summed from 0 to 10, with high scores indicating greater knowledge.

Satisfaction

The five items of the Patient Satisfaction Questionnaire (PSQ) will be used to measure satisfaction. Lower scores indicate higher satisfaction. [Blanchard et al., 1986]

Quality of communication

The 11 items on the quality of communication in the Health Information National Trends Survey (HINTS) will be used to measure quality of communication. High scores indicate greater communication.  [Smith et al., 2015]

Social support

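### The raw PHQ-9 and GAD-7 cut-off rates are screen-positive proportions, yet the protocol reports them as prevalence; by its own accuracy figures a true 10% major depression would be expected to read 19.6%

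*Protocol*

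**What the plan says.** Section 1 of the protocol gives the primary outcome as "Outcome: Prevalence of depression". Section 3.4 says that PHQ-9 "will be used to measure depression", and adds that "a PHQ-9 score ≥10, the cut off score, had a sensitivity of 88% and a specificity of 88% for major depression". For the secondary outcome of anxiety, a GAD-7 score of 10 or more "had a sensitivity of 89% and specificity of 82% for generalized anxiety disorder".

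Section 3.9.1 fixes the estimator: "Estimates of the prevalence of depression, anxiety, and other mental comorbidity in the target population will be reported as unadjusted raw rates", taken over the total sample. The same section then relates other variables to depression and anxiety "depending on the presence or absence of depression and anxiety based on outcome scores".

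Section 3.8 adds a SCID interview for all patients at or above the PHQ-9 cut-off and for a convenience sample of around 20–40 people below it, in order to obtain rates of mental disorder. Nothing in the protocol links those interviews, or the quoted accuracy, to the PHQ-9 or GAD-7 rate.

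**The concern.** No single sentence defines prevalence of depression as the proportion with PHQ-9 ≥10, but sections 1, 3.4 and 3.9.1 together leave little else. Only the questionnaire reaches everyone, its cut-off is given, and cases are defined from scores. The protocol therefore takes a screening cut-off, quotes its error rates, and reports the uncorrected rate as prevalence in the target population.

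A screen with imperfect specificity counts some people without the disorder as cases. When the disorder is uncommon, these false positives outweigh the cases that the screen misses, and the raw rate is too high. A larger sample does not remove this. The figure concerned is the primary result, which readers would quote as the depression rate among patients having genomic profiling and their families. Because the protocol states the estimator and says that it is unadjusted, this is not a detail left open for a separate analysis plan.

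**Working it through.** **The plan's own figure.** The protocol states no expected prevalence or precision, so there is no such figure to reproduce. The sample size is a feasibility count: reading 33 tested patients as a monthly average, 33 × 12 = 396 and 396 × 0.75 = 297, rounded to 300. The 300 is used below only for sampling spread.

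**Inputs.** From section 3.4: PHQ-9 ≥10 with Se = 0.88 and Sp = 0.88; GAD-7 ≥10 with Se = 0.89 and Sp = 0.82. True prevalence p is not given, so a range is shown.

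**Formula.** Expected raw rate = Se·p + (1 − Sp)(1 − p).

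- PHQ-9: 0.88p + 0.12(1 − p) = 0.12 + 0.76p
- GAD-7: 0.89p + 0.18(1 − p) = 0.18 + 0.71p

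| True p | PHQ-9 raw | Ratio to true | True cases among PHQ-9 positives | GAD-7 raw |
|---|---|---|---|---|
| 5% | 15.8% | 3.16 | 28% | 21.6% |
| 10% | 19.6% | 1.96 | 45% | 25.1% |
| 20% | 27.2% | 1.36 | 65% | 32.2% |
| 30% | 34.8% | 1.16 | 76% | 39.3% |
| 50% | 50.0% | 1.00 | 88% | 53.5% |

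The fourth column is 0.88p divided by the PHQ-9 raw rate; at 10% it is 0.088/0.196 = 45%. The bias is zero where p = (1 − Sp)/(2 − Se − Sp): 0.12/0.24 = 50% for PHQ-9 and 0.18/0.29 = 62% for GAD-7. Above those values the raw rate is too low.

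**If the accuracy differs here.** With Se = 0.88 and a true 10%, Sp = 0.80 gives 0.088 + 0.20 × 0.90 = 26.8%, and Sp = 0.95 gives 0.088 + 0.05 × 0.90 = 13.3%.

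**Correcting back.** p = (raw + Sp − 1)/(Se + Sp − 1). Suppose 20% of 300 patients screen positive. The usual 95% half-width is 1.96 × √(0.20 × 0.80/300) = 4.5 points, so the reported interval would be about 15.5% to 24.5%. At 88%/88% the corrected figure is (0.20 − 0.12)/0.76 = 10.5%, which lies outside that interval. With Sp = 0.80 it is (0.20 − 0.20)/0.68 = 0%, and with Sp = 0.95 it is (0.20 − 0.05)/0.83 = 18.1%. Dividing 4.5 by 0.76 gives 6.0 points, but that treats the accuracy as known exactly and is too narrow.

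**Whether the interviews settle it.** Take 300 patients and a true 10%. Expected counts are 26.4 true positives, 32.4 false positives, 3.6 missed cases and 237.6 true negatives. Interviewing 20–40 of the 241.2 screen-negatives would find about 0.3–0.6 missed cases (for example 20 × 3.6/241.2 = 0.3). Unweighted SCID cases would be about 9% of the total sample, but 27–34% of those interviewed. The interviews therefore give no usable prevalence without weights, and a convenience sample supplies none.

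**The case against.** The strongest reply is that the outcome is depression as measured by PHQ-9. The stated aim is psychological distress, section 3.9.1 defines presence from scores, and the 88%/88% refers to major depression, a narrower target. For depression defined as PHQ-9 ≥10 the raw rate is unbiased, and the remaining fault is a label. That much stands, and it is why relabelling is the core of the fix. It does not rescue the text as written, which promises the prevalence of depression in the target population and justifies its cut-off by accuracy for a diagnosis.

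A reader might also infer several stronger points that the documents do not support:

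- *The rate cannot fall below 12%.* That is an expected value at zero true cases and depends on the quoted specificity. With 300 patients and no cases, the observed rate could lie between about 8.3% and 15.7%. At Sp = 0.95 the expected floor is 5%.
- *Most people flagged are false positives.* This holds only where 0.88p < 0.12(1 − p), that is, below a true 12%.
- *Changes over time are shrunk to 76% or 71%.* Those factors apply to differences between proportions with equal accuracy in both groups. Section 3.9.1 plans changes in scale scores and states no comparison of patients' and family members' rates.
- *The study already collects a phase-weighted interview estimate.* It does not. The screen-negatives are a small convenience sample without selection probabilities. Coverage of family members is also unclear, since section 3.8 names patients among the screen-positives and section 3.4 names participants.

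**Conclusion.** The point holds in a limited form. The planned estimator gives the proportion screening positive, and the protocol calls it prevalence of depression and anxiety. On the quoted accuracy, the expected PHQ-9 rate exceeds the true rate of major depression by 10.8 points at a true 5%, 9.6 at 10%, 7.2 at 20% and 4.8 at 30%, falling to zero at 50%. For GAD-7 the excess at a true 10% is 15.1 points.

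This rests on two assumptions. The first is that the quoted sensitivity and specificity apply to people having genomic profiling and to their relatives. The documents do not establish this, and a specificity of 0.80–0.95 moves the excess at a true 10% to between 16.8 and 3.3 points. The second is that true prevalence is below 50%; the protocol gives no figure. The direction is upward across the ranges shown, but the size is not fixed by the documents. The point affects the primary result and can be mended without new data.

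**What to change.** In sections 1, 3.4 and 3.9.1, name the raw figure *proportion screening positive (PHQ-9 ≥10; GAD-7 ≥10)* and keep the word prevalence for the disorder.

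In section 3.9.1, add a misclassification-corrected estimate, (raw + Sp − 1)/(Se + Sp − 1), calculated with the accuracy in section 3.4 and over a stated range of sensitivity and specificity. Its interval should reflect uncertainty in those two values as well as sampling error.

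State that SCID diagnoses are supportive only, for example as the share of interviewed screen-positives in whom the diagnosis is confirmed. They should not be turned into a weighted prevalence while the screen-negatives remain a convenience sample. Make sections 3.4 and 3.8 agree on whether family members above the cut-off are interviewed.

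The cost is wording plus a short calculation on data already planned. The downside is a headline figure that is lower, if true prevalence is below the break-even value, and that has a wider interval.

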# 2. INTRODUCTION

## 2.1. Background and rationale

On May 29th 2019, two cancer genomic profiling, CGP tests were reimbursed in Japan; which were "Onco GuideTM NCC Oncopanel system" and "Foundation One CDx". Recently the testing can be only allowed once in a lifetime for those who are advanced cancer patients with no standard therapy, or those who are advanced cancer patients finished standard therapies. The cost of the testing is very expensive that costs total ¥560,000 JPY, however the potential benefit patients enjoy from the cancer genomic profiling testing is individualized genomically appropriate therapeutics, on a word making precision oncology reality. In some malignancy, they already have companion diagnostic tools to survey one or two specific gene that allows to use genetically target therapy which has higher response rate and long survival benefit, such as EGFR-TKIs in non-small cell carcinoma (Maemondo et al., 2010, Mitsudomi et al., 2010). Even in these cancers with companion diagnostic tools, cancer genomic profiling testing sometimes allows to find rare but very effective actionable gene. Interestingly, about 10-20% of those who underwent testing CGP testing finally led to genetically matched therapies (Sunami et al., 2019). As these statistics shows that the ratio who receive benefit from CGP testing is not so much, the growing expectation and focus is not matching its clinical benefit ratio result in disappointment and mental burden both in cancer patients and their family members. There is research of CGP influence on mental health on breast hereditary cancer from Spain and on breast and cervical hereditary cancer from United States; we Japanese don't have any data on mental influence of CGP testing. Spanish research is multi-centered of 30cites with 187 candidates recruited with 4 times of follow up survey asking anxiety, mental burden (Esteban et al., 2018). Research from United States enrolled 232 patients and surveyed psychological impact, understanding (Lumish et al., 2017). Both of the research is focused on only hereditary cancers using germ cell cancer panels and suggest some negative impact toward mental health. They did not show the prevalence rate, clinical course, relative factors nor impact toward family members. Our research focus on not only germ cell mutation but also somatic mutation in CGPs. Moreover, 167 hospitals are selected to perform CGP in Japan, taking account of more limited hospital running clinical trials, there is surely difficulties to access the cites of clinical trials if patients luckily found to have rare actionable genomic alteration. According to Townsley & Selby（2005）'s report that reviewed the preventing factors of cancer patients who had difficulties to be enrolled to clinical trial, revealed that lack of social support had highly impacted against enrollment  It goes without saying that social support will be essential issue for patients with rare actionable mutation to be enrolled to genetically matched clinical trial. To make long story short, our study focusing to reveal the reality of patients and family members who underwent CGP testing toward longitudinal mental and psychological impact, social support, and QOL is essential for accurate and precise understanding of cancer patients with CGP testing.

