### 3.7.2. Retention

**Participant Withdrawal**

Participants, both patients and family members, may withdraw from the study for any reason at any time. The investigator also may withdraw participants from the study in order to protect their safety and/or if they are unwilling or unable to comply with required study procedures after consultation with protocol Chair.

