## 3.8. Data management

Participants will be asked to complete a questionnaire using an electronic patient reported outcome (ePRO) application software or hard copy at baseline (T0), 1 to 4 weeks after receiving the results of CGP testing (T1; approximately 2–3 months post baseline), 3 months (T2) after T1, and 6 months (T3) after T1. These timeframes have been chosen to allow the impact of the test results to be captured in both the short term (when a treatment decision is being made) and longer term (while undergoing or close to completion of the targeted therapy, if adopted). All patients with a PHQ-9 score at the cutoff point of 10 or above (total score) as well as a small subset of participants (around 20–40) selected as a convenience sample who score below this cutoff point will be interviewed using the Structured Clinical Interview for DSM-V-RV (SCID), which includes items on mood disorders, neurotic, stress-related and somatoform disorders, and behavioral syndromes associated with physiological disturbances and physical factors, at each assessment time-point to determine the 4-week and lifetime prevalence rates of comorbid mental disorders

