### 3.9.3. Analysis population and missing data

N/A

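### Missing data and analysis population are marked not applicable, so T2 and T3 prevalence and change would describe only participants alive and responding, with no correction for selective non-response

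*Protocol*

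**What the plan says.** - **Outcome.** The Trial Summary (Section 1) gives the primary outcome as prevalence of depression at four time-points. Section 3.4 measures it with the PHQ-9 and states that "a PHQ-9 score ≥10, the cut off score, had a sensitivity of 88% and a specificity of 88% for major depression".
- **Estimators.** Section 3.9.1 says that prevalence estimates "will be reported as unadjusted raw rates observed in the total sample". For the scales it says "Temporal changes in scales will be investigated by calculating differences between time-points".
- **Missing data.** Section 3.9.3 is headed "Analysis population and missing data". Its whole content is N/A.
- **Selection check.** Section 3.9.1 opens with: "To examine the possibility of selection bias, a comparative analysis of respondents and non-respondents will be conducted based on demographic and clinical data".
- **Population.** Section 2.1 says testing is allowed only for "advanced cancer patients with no standard therapy, or those who are advanced cancer patients finished standard therapies".
- **Timing.** Section 3.8 places the second assessment at "T1; approximately 2–3 months post baseline", with T2 and T3 at 3 and 6 months after T1.
- **Withdrawal.** Section 3.7.2 lets the investigator, after consulting the protocol Chair, withdraw participants to protect their safety and/or "if they are unwilling or unable to comply with required study procedures".

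**The concern.** The protocol has a section for missing data and declares the subject not applicable. In this population some patients will very probably die or become too ill to answer before T2 or T3, and no section says how either event is handled. The total sample named in Section 3.9.1 therefore has no defined meaning at the later time-points.

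Death and non-response are different problems. A patient who has died has no PHQ-9 score, so death calls for a clear statement of whom the rate describes. A living patient who does not answer has a score that was not observed. If depressed patients answer less often, the raw rate among respondents is too low; if they answer more often, it is too high.

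At stake is the trajectory from T0 to T3. A change in prevalence between those points could be a real change, a change in who is still alive, or a change in who still answers. The plan as written cannot tell these apart.

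**Working it through.** **1. Length of follow-up (Section 3.8).** T0 to T1 is about 2 to 3 months and T1 to T3 is 6 months, so T0 to T3 is 2 + 6 = 8 to 3 + 6 = 9 months. Section 3.7.1 counts T2 and T3 from receipt of the result instead, which shortens this by 1 to 4 weeks and changes nothing below.

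**2. The plan's own numbers (Section 3.6).** 33 × 12 = 396 patients a year; 396 × 0.75 = 297, against 300 stated. For families, 300 × 0.80 × 0.80 = 192, as stated, with a recruitment target of 200. These reproduce. They concern recruitment only and make no allowance for death or loss.

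**3. How many could be observed at T3.** The protocol gives no survival figure. Assuming exponential survival with a median of 6 to 12 months, the share alive runs from 0.5^(9/6) = 35% to 0.5^(8/12) = 63%, that is 300 × 0.35 = 105 to 300 × 0.63 = 189 patients. This shows only why the total sample is not available; it is not a bias.

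**4. Bias in prevalence from non-response among the living.** All inputs are assumed. Let P be the true T3 prevalence among patients alive, L the share of them not responding, and RR the risk of non-response in depressed relative to non-depressed patients. Then

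- non-response if not depressed: l0 = L / (P × RR + 1 − P)
- non-response if depressed: l1 = RR × l0
- observed rate among respondents: P × (1 − l1) / (1 − L)

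Worked case, P = 25%, L = 40%, RR = 1.5: l0 = 0.40 / 1.125 = 0.356; l1 = 0.533; observed = 0.25 × 0.467 / 0.60 = 19.4%.

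| L | RR 1 | RR 1.25 | RR 1.5 | RR 2.0 |
|---|---|---|---|---|
| 20% | 25.0% | 23.9% | 22.9% | 21.2% |
| 40% | 25.0% | 22.1% | 19.4% | 15.0% |
| 60% | 25.0% | 18.4% | 12.5% | not used (l1 = 96%) |

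The bias is zero at RR = 1, about −1 to −13 points across the other cells used, and positive if RR is below 1. For scale, if no patient died, 300 × 0.60 = 180 responders would give a 95% half-width of 1.96 × √(0.194 × 0.806 / 180) = 5.8 points, about the size of the bias in the worked case (−5.6 points).

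With nothing assumed about non-responders, the worked case gives bounds of 0.194 × 0.60 = 11.7% to 11.7% + 40% = 51.7%.

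**5. Bias in change.** Assume a true mean worsening of +1.0 points, SD 4, and a correlation of 0.3 between worsening and the tendency not to respond. The mean among responders is 1 − 4 × 0.3 × φ(z) / (1 − L), where φ is the standard normal density and z the standard normal quantile at 1 − L. This gives +0.58, +0.23 and −0.16 at L = 20%, 40% and 60%. Simulation gave the same values. The sign can reverse.

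**6. What the planned safeguards do.** The respondent comparison describes the selection; the rates remain unadjusted. The regression in Section 3.9.1 is for confounders and predictors and does not address missing outcomes.

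**The case against.** **Scope.** Missing-data methods are often left to an analysis plan, which is not shown here, and N/A appears in several other sections, so it may be a template entry. That would excuse silence. Here the protocol states that the topic does not apply and also fixes unadjusted estimators, and following that text produces the problem.

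**Evidence of loss.** The eligibility criteria set no stage or line of therapy; the description of advanced disease is in the background section. No attrition or death rate is given, and if non-response is unrelated to depression there is no bias. This stands: the protocol supports the exposure to bias but not any particular size or direction.

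**Stronger readings that the text does not support.**
- A reader might infer that later results describe only the fittest survivors. The text supports only those alive and responding; that they are fitter is plausible but nowhere documented. The withdrawal rule is discretionary and does not say that a missed questionnaire ends follow-up.
- A reader might take differences between time-points to mean complete pairs only. That is natural but not stated; differences of summaries are also possible. Pairing removes the shift in case mix but not selection on the change itself (step 5).
- A reader might suspect regression to the mean from grouping by depression. Section 3.9.1 uses that grouping for associations between variables, not for change scores.
- A reader might divide by everyone enrolled, so that missing patients count as not depressed. Nothing in the protocol says so.
- A reader might count all loss, including death, as bias. If the target is prevalence among those alive, death is not bias.

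**Conclusion.** The point holds in a limited form. Section 3.9.3 is wrong to mark missing data as not applicable in this population over about 8 to 9 months, and Section 3.9.1 leaves the denominator undefined at T2 and T3. Prevalence and change at those visits would describe participants alive and responding, and would be biased if non-response among the living depends on depression. The respondent comparison can detect this but cannot repair it.

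No size can be computed from the protocol. At an assumed true prevalence of 25%, non-response of 20% to 60% and a relative risk of non-response of 1.25 to 2.0 (up to 1.5 at 60%), the raw rate would be low by about 1 to 13 points. The figures rest wholly on those assumptions and refer to patients. For family members the likely routes of loss are bereavement and withdrawal. A fall in raw prevalence after testing should not be read as recovery, but neither does the protocol show that such a fall would be an artefact.

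**What to change.** Replace N/A in Section 3.9.3, and amend Section 3.9.1 to match:

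1. **Denominator.** At each time-point, participants alive at that time. Tabulate deaths and missing questionnaires separately.
2. **Prevalence in patients.** At T1 to T3, report the raw rate among respondents alongside a rate weighted by the inverse probability of responding among those alive, modelled on T0 PHQ-9, performance status and stage. Section 3.4 and the T0 questionnaire already supply these.
3. **Prevalence in family members.** Use the same approach with their own baseline variables; patient stage and performance status do not carry over as their own characteristics.
4. **Change in scales.** Fit a likelihood-based repeated-measures model to all observed data, with T0 as either an outcome or a covariate but not both. State that results refer to those alive at each time-point, since such a model would otherwise extrapolate scores past death. Unweighted GEE is not an equal substitute when loss depends on the outcome.
5. **Sensitivity.** Add an analysis that varies the assumed depression rate among living non-respondents, with the bounds in step 4 of the working as its extremes.

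Cost: modest extra analysis and somewhat wider intervals at T2 and T3. It is not only a wording change: vital status is not among the data listed in Section 3.4, so a check of the hospital record is needed for patients, and whether family members are alive also needs a source.

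### Section 3.9.1 ties the association analyses to the PHQ-9 and GAD-7 case split and does not make the total score the main outcome for predictors, so analyses done on the split lose power

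*Protocol*

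**What the plan says.** Section 3.4 describes both instruments as graded and gives each a case-finding threshold. For depression: "Higher scores indicate greater possibility of major depression (a PHQ-9 score ≥10, the cut off score". For anxiety: "a GAD-7 score ≥10 had a sensitivity of 89% and specificity of 82" per cent. The support given for each cut is its diagnostic accuracy. The trial summary in section 1 makes the prevalence of depression the primary outcome.

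Section 3.9.1 then covers several tasks in consecutive sentences:

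- Change over time: "Temporal changes in scales will be investigated by calculating differences between time-points".
- Group comparisons: "Comparisons of demographic and other factors will be conducted using the t-test and ANOVA, and Kruskal-Wallis test", with no outcome named.
- Associations: correlation, chi-squared tests and "regression analysis, depending on the presence or absence of depression and anxiety based on outcome scores", which ties these analyses to case status for depression and anxiety.
- Adjustment and prediction: "Multiple or logistic regression analysis will be used to adjust for the effects of confounders and to identify predictors of outcome", with no statement of which outcome goes with which model.

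Section 3.6 plans 300 patients and 200 family members (192 by its own derivation) on feasibility grounds. It states no power, effect size or expected prevalence.

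**The concern.** A prevalence needs a yes/no definition, and using the cut for that purpose is not in dispute. Asking which factors go with more or less distress is a different task. Once the scores are split at 10, a PHQ-9 of 0 and one of 9 count as the same, while 9 and 10 count as opposites. Diagnostic accuracy justifies a threshold for finding cases. It does not make the threshold the best scale for studying correlates.

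The only outcome form that section 3.9.1 names for depression and anxiety in the association analyses is the split. For predictors, it leaves score and split as alternatives on the same variable without ranking them. Two things are at stake. Real but modest correlates of distress, such as social support or quality of communication, may be reported as non-significant. And where both forms are available with neither named as main, the choice can be made after the results are seen.

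**Working it through.** **The plan's own figures.** No power is stated, so there is none to reproduce. The sample sizes follow from section 3.6: 33 × 12 × 0.75 = 297, given as 300; and 300 × 0.80 × 0.80 = 192. Both are used below.

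**Assumptions, not in the protocol.** Two-sided alpha 5%; prevalence at or above the cut of 10%, 20% or 30%; effect sizes as shown.

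**1. Information kept by a cut on a normal score.** For prevalence p and cut point c = z(1−p), the fraction kept is φ(c)² / [p(1−p)].

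| p | c | φ(c) | Fraction kept |
|---|---|---|---|
| 0.10 | 1.282 | 0.1755 | 0.0308 / 0.09 = 0.34 |
| 0.20 | 0.842 | 0.2800 | 0.0784 / 0.16 = 0.49 |
| 0.30 | 0.524 | 0.3477 | 0.1209 / 0.21 = 0.58 |

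At 20% prevalence, 300 patients analysed on the split carry about the information of 300 × 0.49 = 147 analysed on the score.

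**2. Power for a continuous predictor, normal score.** Power = Φ(atanh(r)·√(N−3) − 1.96), with r replaced by r·√(fraction kept) for the split. Example, N = 300 and r = 0.15: 0.1511 × 17.23 − 1.96 = 0.645, so 74%. At p = 0.20, r becomes 0.15 × √0.49 = 0.105, and 0.1054 × 17.23 − 1.96 = −0.144, so 44%.

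| N | r | Score | Split, p = 10% / 20% / 30% |
|---|---|---|---|
| 300 | 0.15 | 74% | 33 / 44 / 50% |
| 300 | 0.20 | 94% | 53 / 68 / 75% |
| 192 | 0.20 | 80% | 37 / 49 / 56% |

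**3. Power for a balanced two-group predictor, normal score.** Choose the difference d that gives the score analysis 80% power at N = 300: d = (1.96 + 0.84) × √(4/300) = 0.323. With overall prevalence 20%, the proportions above the cut are 15.5% and 24.5%. A two-proportion test with 150 per group then has 49% power, a loss of 31 points. At prevalence 10% and 30% the split has 36% and 56%, losses of 44 and 24 points. With score power between 50% and 95% and prevalence between 10% and 30%, the loss is 18 to 44 points at N = 300, and nearly the same at N = 192. Where score power is very low (30%) or very high (99%), some losses fall to 9 to 17 points.

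**4. Skewed scores.** PHQ-9 totals are likely to be right-skewed, so the comparison was repeated by simulation with negative binomial scores capped at 27 (an assumed maximum; the protocol does not print the range).

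- Groups differing by a multiplicative shift in mean, 150 per group, prevalence about 10% to 27%: the split loses about 10 to 23 points against a t-test and about 5 to 14 against a rank test. One example, at prevalence 18%: t-test 64%, rank test 56%, chi-squared 46%.
- A continuous predictor linked to the score by a Gaussian copula, correlation 0.15 to 0.20, prevalence 13% to 29%, N = 300 and 192: the split loses 17 to 34 points against a linear test. At N = 300, prevalence 21% and correlation 0.15, power is 68% against 43%. A repeat run gave 14 to 33 points.
- Other choices of mean, dispersion and predictor type widened the range to about 8 to 48 points.

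The models differ because a multiplicative shift acts mostly on the upper tail, where the cut lies, so the cut keeps more of the signal.

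**The case against.** The strongest objection is that section 3.9.1 does not confine itself to the split. Correlation is named in the association sentence. Multiple regression, set beside logistic, ordinarily means a linear model on a numeric outcome. The t-test, ANOVA, Kruskal-Wallis test and changes in scale scores are planned as well. A reader might infer that the split replaces the scores throughout. The text does not support that, and a linear model on the total score is already permitted. It remains true that the split is the only form named for depression and anxiety in the association sentence, and that nothing makes the score the main outcome for predictors.

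Second, matching outcomes to models is often left to a statistical analysis plan, and none is shown here. An open choice alone would therefore be no finding. The association sentence, however, is a method stated in the protocol, and it points to the weaker form.

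Third, studying case status is coherent, since the primary outcome is a prevalence and the PHQ-9 cut also selects patients for diagnostic interview. This is a good reason to keep the logistic model as a supporting analysis. It does not make that model the more informative one for finding correlates.

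Fourth, the size of the loss depends on assumptions. This stands. A single figure such as 20 to 40 points cannot be defended, because skew and effect size move the loss well outside that range.

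A reader might also infer that the logistic model would be overfitted, by counting every listed factor against the expected cases. The protocol never says that all of them enter one model. Several are listed as secondary outcomes, and several clinical items are described only for patients. That inference is not supported.

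**Conclusion.** The point holds in a limited form: the protocol steers the association analyses to the split and does not rank the score first for predictors. On an assumed normal score, a cut at 10% to 30% prevalence keeps about 34% to 58% of the information and costs about 20 to 45 points of power when the score analysis has 50% to 95% power. On skewed scores the cost is roughly 5 to 40 points, with single scenarios somewhat above. These figures rest on assumed prevalence, effect size, alpha and score shape, none of which the protocol gives. They apply only to analyses actually run on the split. The primary prevalence estimate is unaffected. The loss is material in nearly all scenarios and the remedy is cheap, so the change should be made.

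**What to change.** In section 3.9.1, state three things:

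1. The cut at 10 on PHQ-9 and GAD-7 is used to report prevalence.
2. Associations with, and predictors of, depression and anxiety are analysed mainly with the PHQ-9 and GAD-7 total scores as outcomes in multiple linear regression, with robust or bootstrap standard errors because the scores are likely to be skewed.
3. Logistic regression on the cut is reported as a supporting analysis.

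The cost is one or two sentences, with no new data or participants. The downside is small: coefficients are in score points rather than odds ratios, and the scores are skewed. The supporting logistic model supplies the odds ratios, and the robust or bootstrap standard errors address the skew.
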